### Sample size

We estimated our sample size using GPower (version 3.1.9.7) and focused on a meaningful change from baseline to six-months on the primary outcome PTSD symptom severity via a t-test means difference between two dependent means. The expected mean change in PTSD symptom severity as measured by the PCL-C was based on findings from research conducted by the first author in which PSWs implemented SS to a similar population (36). Assuming a moderate effect size, with an alpha = 0.05, and power = 0.80 the GPower analysis determined that a total sample size of 101 would be needed.

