**Methods:**

We are using a Type 1 hybrid implementation design with a non-randomized approach (ISRCTN registration # ISRCTN33100750). We aim to enroll 110 adults (
≧18
) who screen positive for unhealthy use of alcohol, prescription medications (used nonmedically) and/or illicit drugs. Peer support workers are responsible for screening, using MI to increase engagement in screening and treatment and delivery of SS. Pharmacotherapy is provided by addiction clinical specialists. Treatment is provided post hospital discharge via telehealth to increase access to care. Participants are identified through (1) review of electronic health records for individuals with a chief or secondary complaint or mental health condition relating to alcohol and/or other drug use, (2) referrals from clinical staff and (3) screening in the ED and medical inpatient units. Feasibility is being measured through process data. Effectiveness will be determined by changes in two primary outcomes: (i) PTSD symptom severity; and (ii) substance use.

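### The sample size of 101 does not follow from a paired t-test with a moderate effect, alpha 0.05 and power 0.80: effect label, power and N cannot all be right

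*Protocol article*

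**What the plan says.** The Sample size section names the software (GPower 3.1.9.7) and the test, "via a t-test means difference between two dependent means". The calculation "focused on a meaningful change from baseline to six-months" in PTSD symptom severity.

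The effect is given in words only: "Assuming a moderate effect size". On its origin the section says: "The expected mean change in PTSD symptom severity as measured by the PCL-C was based on findings from research conducted by the first author". No mean change, SD of change, correlation or standardised effect is printed.

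Effect, error rates and result stand in one sentence, which assumes a "moderate effect size, with an alpha = 0.05, and power = 0.80 the GPower analysis determined that a total sample size of 101" would be needed. It does not state one or two tails.

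The Methods paragraph of the Abstract sets the recruitment target: "We aim to enroll 110 adults". The analysis section on effectiveness speaks of significant change and of paired t-tests, and declares no one-sided test.

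**The concern.** Test, alpha, power and resulting N are all stated, and the effect is given a conventional label, so the calculation can be checked. A paired t-test is efficient, and an N above 100 at 80% power points to an effect well below what is normally called moderate.

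This is the only sample size justification in the article, and a reader needs it to judge what the study can detect. If the effect really is moderate, 80% understates the power by a wide margin. If the effect entered was about a quarter of an SD, the label overstates the change the study was built to find, and the 80% holds only for a one-sided test that the article never declares.

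**Working it through.** **Inputs.** From the Sample size section: paired t-test, alpha 0.05, power 0.80, N = 101. Not given: number of tails (both tried) and the numeric effect. Assumption: moderate means dz = 0.5, where dz is the mean change divided by the SD of change. The range 0.25 to 0.5 is shown.

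**Formula.** With n pairs, the test statistic is noncentral t with n − 1 degrees of freedom and noncentrality dz·√n. One-sided power is 1 − F(t₀.₉₅). Two-sided power is 1 − F(t₀.₉₇₅) + F(−t₀.₉₇₅). Here F is the noncentral t distribution function, and the required n is the smallest one with power of at least 0.80.

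**Step 1: the stated inputs at dz = 0.5.**
- Two-sided, n = 34: noncentrality 0.5 × √34 = 2.915, critical t (33 df) 2.035, power 0.808. At n = 33 the power is 0.795. Required n = **34**.
- One-sided, n = 27: power 0.812. At n = 26 it is 0.798. Required n = **27**.
- Normal-approximation check, two-sided: ((1.960 + 0.842)/0.5)² ≈ 31.4, consistent with 34 after the t correction.

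The stated 101 is not reproduced.

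**Step 2: other values of dz (alpha 0.05, power 0.80).**

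| dz | n two-sided | n one-sided |
|---|---|---|
| 0.5 | 34 | 27 |
| 0.4 | 52 | 41 |
| 0.3 | 90 | 71 |
| 0.25 | 128 | 101 |

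Nothing from 0.3 to 0.5 reaches 101.

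**Step 3: other readings of the same sentence.**
- If moderate means d = 0.5 on the raw-score SD, then dz = 0.5/√(2(1 − r)). At r = 0, dz = 0.354 and n is 65 two-sided or 51 one-sided. At r = 0.3, n is 46 or 37. At r = 0.5, n is 34 or 27.
- If 101 already included an allowance for loss, 34/(1 − loss) = 101 would require a loss of 1 − 34/101 = 66%. The separate target of 110 suggests instead that 101 is the figure before any allowance.

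**Step 4: what gives 101.**
- One-sided, dz = 0.25: noncentrality 0.25 × √101 = 2.512, critical t (100 df) 1.660, power 0.8025. At n = 100 it is 0.799. Required n = **101**.
- Two-sided, dz = 0.282: noncentrality 0.282 × √101 = 2.834, critical t 1.984, power 0.801. At n = 100 it is 0.798. Required n = **101**.

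**Step 5: power at n = 101.**

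| dz | two-sided | one-sided |
|---|---|---|
| 0.5 | 0.999 | >0.999 |
| 0.3 | 0.848 | 0.911 |
| 0.25 | 0.701 | 0.803 |

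**Step 6: illustration under loss.** The article gives no rate of missing interviews, so 20% and 30% are assumptions. From 110 enrolled they leave 110 × 0.80 = 88 and 110 × 0.70 = 77. Two-sided power is then 0.64 and 0.58 at dz = 0.25, and above 0.99 in both cases at dz = 0.5. Without knowing dz, the effect of any loss cannot be judged.

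**The case against.** The strongest defence is that *moderate* is not a number. The section ties the expected change to an earlier study, so the authors may have entered an effect derived from that study and described it loosely. The error would then be one word, with N and power correct. A journal article may also leave the mean change, the SD and the number of tails to the full protocol. Both points stand in part. The value dz = 0.5 is an assumption, and the missing inputs are not in themselves the fault. What remains is that the printed label and the printed N conflict, and the conflict persists down to dz = 0.3.

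Three stronger readings may tempt a reader, and the article supports none of them.

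- *That the trial was sized with an undeclared one-sided test at dz = 0.25.* That pair matches 101, but it is back-solved; two-sided dz of about 0.282 matches equally well. Like must also be compared with like: 34 against 128 two-sided, or 27 against 101 one-sided.
- *That 34 participants would be enough, so slow enrolment does not matter.* The 34 applies to an unadjusted paired t-test at dz = 0.5. The planned analysis is a multilevel regression with a long list of control variables, three predictors and any significant secondary outcomes.
- *That poor retention already undermines 101 out of 110.* The Discussion reports difficulty keeping people in treatment, which is not the same as missing research interviews. The section on participant interviews describes payments, repeated contact by several channels and phones to support follow-up.

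Sizing the study on one of its two primary outcomes is openly stated and is a common choice. It is not part of this point.

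**Conclusion.** The sample size statement is wrong as written: a paired t-test, a moderate effect, alpha 0.05, power 0.80 and N = 101 cannot all be true. At the conventional dz = 0.5 the stated N is about three times the two-sided requirement (101/34 ≈ 3.0), and power at that N is above 0.99, not 0.80. If N and power are right, the effect is about 0.25 one-sided or 0.28 two-sided, nearer small than moderate.

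The numbers 34 and 27 rest on dz = 0.5. The mismatch does not, since it holds for every dz from 0.3 to 0.5 and for d = 0.5 on the raw-score scale at correlations of zero or above. The article does not show which input was misreported. It also does not follow that the study is underpowered: 101 is ample for a truly moderate change in this test, and falls to two-sided power of 0.70 only if the true value is dz = 0.25.

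**What to change.** Recover the GPower entry and restate the paragraph with the dz actually used and the number of tails, preferably with the mean PCL-C change and SD of change behind it. Then correct whichever element is wrong:

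- if dz was about 0.25 to 0.28, drop the word moderate;
- if dz was about 0.5, correct the N or the stated power.

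If testing is two-sided, the sentence can read that 101 evaluable participants detect a standardised change of about 0.28 with 80% power. Any power shown for losses from the 110 enrolled should be labelled as an assumption.

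The cost is one re-run and one corrected paragraph. No extra enrolment is needed and no study procedure changes. The restated figure may look better or worse than the present one, depending on which input was used.

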## Methods: data collection, management and analysis

Data collection consists of activity logs completed by project personnel, surveys completed by hospital personnel, participant interviews, and extraction of patient-level data from medical records.

### Activity logs

To determine the feasibility of our intervention, process data are being collected by project personnel via activity logs on the number of (1) brief screenings, (2) TAPS, (3) referrals from hospital staff, (4) individuals determined eligible for SUD care, (5) individuals who engage in treatment and type of treatment (i.e., SS and/or pharmacotherapy), and (5) the number of SS and/or pharmacotherapy sessions completed.

### Surveys completed by hospital staff and PSWs

To further our understanding of feasibility, we are also collecting data from hospital personnel on perceived acceptability, appropriateness, and feasibility of the screening component of our intervention. Acceptability refers to how those targeted and involved in implementing the program react to the screening. Appropriateness refers to the extent to which the screening fits within the ED and medical inpatient settings. Feasibility refers to the extent to which the screening can be successfully implemented within the ED and medical inpatient settings. These constructs will be measured by three established self-report measures: the (i) Acceptability of Intervention Measure (AIM), (ii) Intervention Appropriateness Measure (IAM), and (iii) Feasibility of Intervention Measure (FIM). The AIM, IAM and FIM include 4 items rated on a 5-point Likert scale ranging from “completely disagree” to “completely agree” (53). Higher scores indicate higher perceptions of acceptability, appropriateness, and feasibility. The measures take approximately one minute each to complete. They will be completed online by PSWs on the study team and all providers within the ED and inpatient settings, including nurses, emergency physicians, inpatient physicians and other clinical support staff. Since these instruments were not designed to be completed by those who receive the intervention, we intentionally included the Client Satisfaction Questionnaire-8 [75} as part of the battery of measures (see **Table 1**) to provide an opportunity for participants enrolled in the study to voice their opinions about the acceptability of the intervention.

### Participant interviews and consent

Once an individual agrees to engage in treatment, the PSW provides details about the opportunity to participate in a prospective follow-up cohort study. Individuals who are interested in participating sign a release of information agreeing to be contacted by a member of the research team. A member of the research team is then responsible for contacting individuals to provide further information about the study, obtaining consent for those who agree to participate and conducting baseline and follow-up interviews. Follow-up interviews are being conducted every 60-days post baseline. The consent process and all data collection is conducted by phone or a HIPAA compliant video conferencing platform. Individuals are compensated for their participation in the study with a $60 merchandise gift card for completing the baseline interview and $90 for every follow up assessment. The research team makes multiple attempts at varied times of the day and day of the week to consent individuals and complete baseline and follow up interviews. Participants are contacted via phone, text, mail and email. Participants are also offered a phone with monthly cell phone service to increase the likelihood of their participation in the study. Interviews range between 45 and 60 minutes. **Table 1** provides an overview of all data being collected during participant interviews, including the data collection tools and time point.

### Data management

Participants are assigned a participant ID number at the first stage of data processing. The participant ID number is then added to an excel file which links the participant’s identifying information to their corresponding ID number. The excel file is kept on password protected computers and the linking information will be deleted at the end of data collection. Data are never directly linked to participant identifying data. Only research team members have access to the participant ID numbers. All data are entered into a REDCap database. The REDCap database is also password protected and only the research team has access to the data. All data will be maintained and archived or destroyed for six years after the study closes then will be destroyed.

### Statistical methods

#### Feasibility

To evaluate the feasibility of our intervention, we will create a scale value for each the AIM, IAM and FIM by averaging responses. We will also summarize the number and corresponding percentages of (i) brief screens and TAPS completed, (ii) individuals determined eligible, (ii) individuals determined ineligible and reasons for ineligibility, (iii) individuals who agree to participate in treatment, (iv) types of services individuals agree to (SS and or pharmacotherapy for SUD), (iv) types of services individuals engage in, (v) SS and pharmacotherapy sessions completed. For all of these data points, we will also stratify data by gender, ethnicity, race and primary substance of use.

#### Effectiveness of the multi-level intervention

Two primary outcomes will inform our assessment of effectiveness: change in PTSD symptom severity [as measured by the Post-Traumatic Symptom Checklist (44)] and change in substance use [as measured by the Addiction Severity Index (45)]. We will use a pre-post intervention multilevel regression model analysis to examine the change in our primary outcomes of interest. The goal of the multilevel models will be to look for significant and meaningful change in the pre-post scores of our primary outcomes, PTSD symptom severity and substance use, based on the impact of the client’s predictor variables; criminal justice involvement, motivation to change and client treatment satisfaction (see **Table 1**).

To assess the impact of our covariates and secondary outcomes of interest, we will apply a multi-step approach to examine the significance of our independent variables. First, we will test for significant pre-post differences in our secondary outcomes to assess the impact of the variables from the start to finish of the client’s time in the program using parametric paired t-tests. Results of the paired tests will provide results to the significance of the impact pre-post on the client’s perceptions of the program and will provide validation of using the markers as covariates in the regression model. Second, we will apply two change-score multilevel regression models; one for the PTSD symptom severity outcome and one for the substance use outcome, with control variables (age, race, ethnicity, gender, relationship status, level of education, income level, employment status, health insurance status, provider and housing status), significant secondary outcome variables (quality of life, past barriers to substance use treatment, perception of recovery, self-stigma, substance craving, emergency department utilization and hospital treatment facility utilization) and predictor variables mentioned above. Examination of the multilevel regression model will allow for examination of client level deviation of the outcome variables by the time and predictor variables. *Post-hoc* analysis of the correlation matrix and pairwise t-tests of secondary outcomes and pre-post measurement will be examined to understand the impact of the markers in relation to the full scale of the data. Models will be used to assess for statistical robustness using the variance inflation factor for multicollinearity and appropriate error distribution tables. Latent-trait variables will be assessed for internal validity using exploratory factor analysis and reliability using Cronbach’s Alpha measure of internal consistency. While the primary outcome endpoint will be 120 days post-baseline, we will conduct secondary analyses to examine outcomes for participants using the last follow-up date post-baseline.

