## Methods: participants, multi-level intervention, and outcomes

### Study design

This study uses a Type 1 hybrid implementation design with a non-randomized approach (30) (see **Figure 1**). While the primary focus of our study is to test the intervention, we are also very interested in understanding implementation related factors. As a result, we are collecting process data along every step of **Figure 1**, including for example, the number of referrals and patients screened, number of patients determined eligible and reasons for ineligibility, number of patients who agree to treatment and attend at least one appointment.

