### Outcomes

**Table 1** provides an overview of our primary, secondary and other outcomes, including the specific tool used to measure the outcome and measurement time point.

**Table 1 T1:** Overview of data collection.

Domain	Data Collection Tool	Time Point	Variable Type
Post-Traumatic Stress Disorder Symptom Severity	PTSD CheckList – Civilian Version (PCL-C) (44)	Baseline and every 60 days	Primary Outcome
Substance Use	Addiction Severity Index (45)	Baseline and every 60 days	Primary Outcome
Demographics	Age, race, ethnicity, gender (assigned at birth and current identity), relationship status, level of education, income level, employment status, health insurance status and provider, housing status	Baseline evaluation	Covariates
Criminal Activity Involvement	Criminal Justice Questionnaire (developed by first and second author)	Baseline and every 60 days	Secondary Outcome and Predictor
Motivation to Change	The Change Questionnaire (46)	Baseline and every 60 days	Secondary Outcome and Predictor
Treatment Satisfaction	Client Satisfaction Questionnaire (CSQ-8) (47)	Baseline and every 60 days	Secondary Outcome and Predictor
Quality of Life	36-Item Short Form Survey Instrument (SF-36) (48)	Baseline and every 60 days	Secondary Outcome and Covariate
Past Barriers to Substance Use Treatment	Barriers Questionnaire (49)	Baseline and every 60 days	Secondary Outcome and Covariate
Perception of Recovery	The Questionnaire about the Process of Recovery (QPR) (50)	Baseline and every 60 days	Secondary Outcome and Covariate
Self-Stigma	Substance Abuse Self-Stigma Scale (51)	Baseline and every 60 days	Secondary Outcome and Covariate
Substance Craving	3-Item Substance Craving Scale (52)	Baseline and every 60 days	Secondary Outcome and Covariate
Emergency Department Utilization	Services Use Questionnaire and EHR (developed by first and second author)	Baseline and every 60 days	Secondary Outcome and Covariate
Hospital and/or treatment facility utilization	Services Use Questionnaire and EHR (developed by first and second author)	Baseline and every 60 days	Secondary Outcome and Covariate

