The third challenge is the difficulty in engaging and retaining individuals in treatment. Challenges to substance use treatment engagement and retention are common (74, 75). In this particular study, while the participants have presented to the ED for injuries or illness related to the SUD (e.g., cirrhosis, pancreatitis), they may or may not make this connection and therefore may not be considering treatment for SUD. This could have a subsequent impact on their motivation for change, especially during the contacts that occur after their hospital encounter. It is also possible that within the initial meeting the PSWs do not have the opportunity to establish adequate rapport to assure that the relationship is of enough importance to ensure participant’s continued investment in further interactions. Examples of variables that may have impacted this are length of time the individual had been in the ED or inpatient unit, and the patient’s lack of alertness - due to intoxication and/or medications - during conversations with the PSW. This may account for some participants reportedly not remembering who the PSWs are when they are contacted post discharge and showing a reluctance to engage. Research on barriers to substance use treatment is extensive, with a recent overview of systematic reviews reporting 37 structural barriers (e.g., long waiting lists, expensive costs, insufficient options for treatment), 21 individual barriers (e.g., fear of stigma, motivational factors, psychiatric comorbidities), and 19 social barriers (e.g., difficulties with establishing a non-drug use network of friends, no supportive family) (76). There are barriers specific to our target population that are noteworthy. First, given that individuals are being recruited from the ED or medical inpatient, once discharged they are likely dealing with complex health and life circumstances that take priority over SUD treatment (77). Second, our intervention is based in a hospital that serves rural and tribal communities, and in both of these communities stigma, misinformation, mistrust and the lack of anonymity discourages individuals from seeking care (78, 79). Third, while providing services via telehealth could be perceived as being within the community, it may be that for certain participants, their preference may still be community-based providers and face-to-face interactions, versus this model of care. Finally, some of our patients from rural areas have had difficulty connecting to telehealth services because of not having broadband internet service; a challenge that has been reported in the literature on barriers to telemedicine in tribal communities (80). We have implemented several strategies to reduce barriers to care and hopefully decrease the low engagement and retention in treatment rates. First, when needed, we are providing individuals with cell phones and paid monthly cell phone plans so that they can access care provided via telehealth and to stay in contact with their PSW as well as research team. The phone comes preloaded with contact numbers for their PSW, the 988-crisis line, and Zoom and Teladoc apps to access telehealth appointments. The client has unlimited talk, text and data as long as they are engaging in services. If a client stops responding to calls and messages, they are given multiple reminders to re-engage and after six weeks of non-responsiveness, phone service is discontinued. Second, we are contacting patients multiple and various times throughout the day to schedule their appointments and are even willing to meet with patients after regular business hours if need be.

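### Both primary models include treatment satisfaction as a fixed predictor although enrolment does not require attendance, so the primary estimate is conditioned on a perception that depends on engagement

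*Protocol article*

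**What the plan says.** The Statistical methods part of the protocol article (Effectiveness of the multi-level intervention) states the goal of the multilevel models as finding change in PTSD severity and substance use in relation to "criminal justice involvement, motivation to change and client treatment satisfaction". It continues: "we will apply two change-score multilevel regression models; one for the PTSD symptom severity outcome and one for the substance use outcome". Three groups of terms enter: demographic controls, those secondary outcomes found significant in paired tests, "and predictor variables mentioned above". Treatment satisfaction belongs to the third group and is absent from the list that is screened. The primary endpoint is set at 120 days after baseline.

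Table 1 (Outcomes) schedules the CSQ-8 satisfaction form at baseline and every 60 days, as a secondary outcome and predictor. The section on surveys completed by hospital staff and PSWs says the form was included "to provide an opportunity for participants enrolled in the study to voice their opinions about the acceptability of the intervention".

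On entry to the cohort, Participant interviews and consent says: "Once an individual agrees to engage in treatment, the PSW provides details about the opportunity to participate in a prospective follow-up cohort study". Study design lists among its process data the "number of patients who agree to treatment and attend at least one appointment", so agreeing and attending are treated as separate steps. The Discussion reports: "The third challenge is the difficulty in engaging and retaining individuals in treatment".

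**The concern.** The article's objective covers an intervention meant to link people to treatment and keep them there. The effectiveness estimate should therefore cover those who enrolled and were never linked. Because enrolment precedes attendance, the cohort can contain such people. The research team interviews participants separately from the PSWs who deliver Seeking Safety, so PTSD and substance use scores can exist for someone who attended nothing.

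Satisfaction with treatment is a different kind of variable. Its availability, or what it refers to, depends on whether the person engaged. Making it a compulsory term in both primary models ties the main result to engagement. At worst the result describes only those who were treated. At best it is adjusted for a perception formed after enrolment that does not mean the same thing for every participant.

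**Working it through.** The article reports no figure for this point. The first part therefore compares its statements, and the second shows what size would follow from stated assumptions.

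**Consequences of the stated model**

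1. Satisfaction enters both models unscreened, and no primary regression without it is described.
2. Enrolment follows agreement to treatment, so an enrolled participant with no session is possible.
3. For that participant, a follow-up score is in one of two states:
   - *Missing.* A model containing the term needs some rule to keep the record. If incomplete records are dropped, the outcome score is lost with them. Imputing would mean constructing satisfaction with treatment that did not take place.
   - *Present, but about the hospital contact.* The record stays, but the predictor then measures hospital screening and motivational interviewing for some and telehealth treatment for others. How far this alone moves the average change depends on how the term is coded, which the article does not say. The coefficient in any case mixes two things.

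**Size if records are lost (assumed inputs)**

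Inputs from the article: enrolment target 110 (Abstract) and required sample 101 (Sample size). Inputs assumed: share f who never attend, and a difference D in mean change between attenders and non-attenders, in SD of change. Outcome drop-out is ignored.

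- Shift: attender mean − all-enrolled mean = f × D.
- Records left: n = 110 × (1 − f).
- Standard error of a mean change: 1/√n.

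| f | n left | SE | Shift at D = 0.3 | Shift ÷ SE |
|---|---|---|---|---|
| 10% | 99 | 0.101 | 0.03 | 0.30 |
| 20% | 88 | 0.107 | 0.06 | 0.56 |
| 30% | 77 | 0.114 | 0.09 | 0.79 |
| 40% | 66 | 0.123 | 0.12 | 0.97 |

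At f = 20% and D = 0.5 the shift is 0.10 SD, or 0.10/0.107 = 0.94 SE. The SE must use the records left. With all 110 (SE 0.095) the 40% row would read 1.26, which overstates it.

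**Precision**

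The target exceeds the required sample by 110 − 101 = 9 people, and 9/110 = 8.2%. A 10% loss leaves 99, below 101. The article gives neither a numeric effect size nor sidedness, so 101 cannot be confirmed. In a paired t-test with 80% power it corresponds to a standardised change of about 0.25 (one-sided) or 0.28 (two-sided). At those values power is 0.83 with 110 records, 0.79 to 0.80 with 99, 0.74 to 0.75 with 88 and 0.62 to 0.64 with 66. If moderate meant 0.5, power would still be 0.98 with 66. The point does not depend on this calculation.

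**The case against.** A reader might infer that satisfaction cannot be scored without a session, so that non-engagers necessarily drop out of the primary analysis. The article does not support that, for three reasons.

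- Table 1 schedules the form for participants generally, at baseline as well as follow-up, with no attendance condition. Its stated purpose refers to enrolled participants and to the intervention, which includes hospital screening and motivational interviewing. A never-attender has something to rate.
- The article does not say whether the baseline, follow-up or time-varying score is the predictor. With the baseline score, the missing-score mechanism described here does not arise.
- Deletion of incomplete records is stated nowhere. Missing-data handling may sit in an analysis plan that is not shown, and its absence here is no fault.

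The Discussion also does not say that many cohort members never attended. It says its challenges lowered enrolment in treatment and in the study, so some non-engagement appears as non-enrolment. Consent takes place in a later contact, which may select out more. Those who do not engage may also miss interviews, and for them dropping the satisfaction term recovers nothing. Finally, the article makes the predictors part of its stated goal.

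All of this limits the certainty and size of the harm. It does not remove the stated choice: a term tied to engagement is compulsory in both primary models. Use of a follow-up score is the natural reading of a form meant to capture acceptability of the intervention, though it remains an inference. Interest in satisfaction as a predictor can be served without putting the term in the main estimate of change.

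**Conclusion.** The point holds in a conditional form. The text establishes that satisfaction is a fixed, unscreened predictor in both primary models, that enrolment precedes attendance, and that engagement is acknowledged to be poor. With a follow-up score, the primary estimate is conditioned on a post-enrolment perception that depends on engagement.

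Restriction to engagers is a possible consequence, not a demonstrated one. It needs the score to be missing for non-attenders and their records to be dropped. A shift towards benefit further assumes that non-attenders improved less, which is plausible but not documented. The 0.03 to 0.12 SD range (about 0.3 to 1.0 SE) rests wholly on assumed shares and an assumed 0.3 SD difference. The true size cannot be obtained from the article. The change is worth making because it removes the dependence whichever of these conditions applies.

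**What to change.** Estimate the primary 120-day change in PTSD severity and in substance use in all enrolled participants with an outcome score, using models without the satisfaction term. Report the association with satisfaction in a separate model, labelled secondary and limited to participants who attended at least one session.

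This changes analysis wording only; no data collection is affected. The cost is that the satisfaction association becomes a secondary result and applies to attenders alone.
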